**4.5 Participant Recruitment Procedure**

Participant recruitment will be conducted in collaboration with the Valencian Association of Fibromyalgia Patients (AVAFI), which will disseminate pertinent information via various media to facilitate volunteer enrollment. In addition to a detailed explanation of the research, a specific time will be allotted to address any questions and provide individualized consultations. This approach ensures that potential participants have a thorough understanding of the study and the intervention before making an informed decision about participating

**4.6 Type of Sampling and Randomization**

Participant recruitment and written informed consent will be obtained by physicians from the “Estilo de vida y salud” research group at CEU Cardenal Herrera University. Randomisation will be conducted by an independent researcher using a computer-generated 1:1 sequence with stratified permuted blocks of random sizes (2–4) within eight strata defined by sex (male/female) and FM severity (four FIQR clusters per Pérez-Aranda et al., 2019 [32]). Allocation will be concealed with sequentially numbered, opaque, sealed envelopes (SNOSE) prepared off-site with tamper-evident seals and carbonless copies. After baseline assessment, site staff will open the next envelope in numerical order to assign the experimental group (EG) or control group (CG). The randomisation list will be held by an independent data manager with no role in enrolment or assessment. Any deviation from sequence or envelope integrity will be recorded and investigated. Outcome assessors and the trial statistician will be blinded to group allocation. Participants and intervention providers cannot be blinded due to the nature of immersive VR and will be instructed not to disclose allocation during assessments. Assessments will be performed by personnel without access to scheduling or allocation logs; groups will be labelled A/B until database lock. Unblinding will occur only to address serious safety concerns or protocol deviations with safety implications, following written authorization from the Principal Investigator; all unblinding events will be logged. The allocation list will remain with the independent data manager.

**4.7 Type of Blinding**

This study will be conducted as a single-blind design, in which the evaluators are unaware of participants’ group assignments. This approach minimizes detection bias, thereby ensuring objective outcome evaluation and enhancing the study’s validity.

**4.8 Intervention**

The intervention programme will last a total of six weeks, with two weekly sessions of 60 minutes each. Sessions will take place in AVAFI’s facilities, in a climate-controlled room that meets the necessary space and privacy requirements. Each session will be led by a researcher responsible for ensuring proper exercise execution and participant well-being. The session will be divided into three distinct phases:

- **Warm-Up Phase (5 minutes):**

Joint mobility exercises combined with breathing techniques to prepare the body for physical activity. These exercises will focus on the cervical and lumbopelvic areas and the upper and lower extremities, without additional load.

- **Main Intervention Phase (50 minutes):**

Participants will carry out a therapeutic exercise programme tailored to their group (intervention or control), with intensity regulated through the Borg Scale (6–20). Sessions will be supervised by a researcher to ensure proper exercise execution and participant safety. Exercises are illustrated in Figure 2 and will include trunk flexion, extension, rotation, and side bending in various positions (standing, seated, and lying down). Participants will be instructed to synchronize the concentric and eccentric phases with their breathing to maintain a consistent execution speed.
The programme will focus on exercises using body weight, and starting from the sixth session, ankle weights and some dumbbell exercises will be added. Participants will perform between 1 and 2 sets of each exercise, adjusting intensity and repetitions according to their perceived exertion, assessed using the Borg Scale (6–20), aiming for an intensity range between 13 and 17. During each session, pain intensity (NPRS-11), perceived exertion (RPE), and well-being associated with Virtual Reality will be recorded.

- **Cool-Down Phase (5 minutes):**

Stretching and breathing exercises to reduce muscle tension and promote relaxation. These will include stretches for the lumbar region and lower extremities, along with deep breathing exercises performed in a supine position.

**Intervention Group: Virtual Reality + Exercise**

Participants assigned to this group will perform the aforementioned therapeutic exercise programme while simultaneously using an immersive virtual reality device (HTC Vive Pro). The VR system will modify the patient’s visual and proprioceptive information, allowing them to reduce the perception of movement, thereby improving pain tolerance and body awareness.

**Control Group: Exercise Without Virtual Reality**

Participants in the control group will follow the same therapeutic exercise programme as the intervention group but without using virtual reality technology. The exercises will be identical in terms of type, progression, and load.

 ***Figure 2: Exercise programme with virtual reality.*** *1) Trunk flexion in standing position; 2) Trunk extension in sitting position; 3) Trunk flexion in sitting position; 4) Glute bridge; 5) Crunch; 6) Trunk inclination in standing position; 7) Trunk rotation in lying position 8) Trunk extension in lying position.*

***Figure 3:*** *VR set up and virtual environment.*

4.9 Outcomes and measurement instruments

1. The FIQR is a validated, widely used instrument for assessing the impact of fibromyalgia on patients’ daily lives. It evaluates three key dimensions: functionality (9 items, 0–30 points), symptoms (10 items, 0–50 points), and overall impact (2 items, 0–20 points), yielding a total score from 0 to 100. Higher scores reflect a greater impact of the disease. Each item is rated from 0 to 10, indicating no impairment to maximum impairment. The Spanish version of the FIQR has demonstrated high reliability (Cronbach’s α = 0.91–0.95) and is considered the reference instrument for evaluating the effectiveness of fibromyalgia interventions, given its sensitivity to detect change and its strong support in the scientific literature ^61,62^.
2. The EQ-5D-5L is a validated questionnaire translated into Spanish for assessing quality of life. Developed by the EuroQol Group as an enhancement to the EQ-5D-3L, it evaluates five key dimensions—mobility, self-care, usual activities, pain/discomfort, and anxiety/depression—using five response levels (1 = best health state, 5 = worst health state). It also includes a visual analog scale (VAS) from 0 to 100 for rating overall health status on the day of evaluation. Test-retest reliability ranges from 0.69 to 0.94 (ICC) ^63^, and it is widely employed in fibromyalgia and chronic pain studies for its capacity to provide an objective, comparative assessment of quality of life ^44,51,63–66^.
3. The participants’ levels of anxiety and depression will be evaluated using the Hospital Anxiety and Depression Scale (HADS), a validated instrument for both clinical and non-clinical populations. It consists of 14 items divided into two subscales—Anxiety (HADS-A) and Depression (HADS-D)—each scored from 0 to 21, where higher scores indicate greater severity. The Spanish version has shown high reliability (Cronbach’s α = 0.83–0.86 for anxiety and 0.82–0.84 for depression; ICC = 0.76–0.93) and approximately 80% sensitivity and specificity. In patients with fibromyalgia, it has demonstrated significant concurrent validity with measures of pain and quality of life, making it an appropriate instrument for this population since it evaluates affective symptoms without confounding somatic symptoms of the disease. Given that fibromyalgia is associated with high rates of anxiety and depression, assessing these factors is crucial for understanding the emotional impact of the condition and determining the effectiveness of therapeutic interventions ^69,70^.
4. Sleep quality will be assessed using the Spanish version of the Pittsburgh Sleep Quality Index (PSQI), a validated instrument for measuring sleep quality and patterns over the past month. It consists of 19 items grouped into seven components, yielding a global score from 0 to 21, where higher scores indicate poorer sleep quality. The Spanish version has demonstrated high reliability (α = 0.805; test-retest r = 0.773, p < 0.001) and convergent validity with the FIQR and SF-36. Its use is widely supported in fibromyalgia research, serving as a sensitive tool for detecting sleep disturbances in this population^71,72^.
5. Pain catastrophizing will be evaluated using the Pain Catastrophizing Scale (PCS), a questionnaire designed to measure the tendency toward negative, exaggerated thoughts in response to pain. It consists of 13 items that assess rumination, magnification, and helplessness, each scored from 0 (never) to 4 (always), yielding a total score of 0 to 52, where higher scores indicate greater catastrophizing. The Spanish version has demonstrated high reliability (Cronbach’s α = 0.79; test-retest ICC = 0.84) and retains the original three-factor structure. It has also shown sensitivity to change with an effect size of up to 2, making it a valid and reliable tool in fibromyalgia and chronic pain research. Additionally, it is useful for predicting pain intensity, disability, and response to therapeutic interventions ^73–75^.
6. Central sensitization will be assessed using the Central Sensitization Inventory (CSI), an instrument designed to identify symptoms related to central sensitization and their impact on daily life. It consists of 25 items evaluating widespread pain, fatigue, concentration problems, sensory hypersensitivity, and sleep disturbances, yielding a total score from 0 to 100. Higher scores indicate a greater burden of symptoms, and scores above 40 are considered indicative of a central sensitization syndrome such as fibromyalgia. The Spanish version has shown high test-retest reliability (ICC = 0.82–0.91) and is widely used in chronic pain research, providing an effective measure of central sensitization in various clinical populations ^76^.
7. Nervous system function will be evaluated through Quantitative Sensory Testing (QST), a set of standardized assessments that measure sensory perception and pain modulation using mechanical, thermal, and pressure stimuli. QST examines key parameters such as detection and tolerance thresholds for pressure pain, thermal detection (heat/cold), and the presence of mechanical and thermal hyperalgesia or allodynia, thus distinguishing between peripheral and central sensitization. Test-retest reliability varies by parameter (ICC = 0.75–0.95), and QST has been validated in fibromyalgia and chronic pain studies. It is a critical tool for characterizing dysfunctions in pain modulation and for assessing the effectiveness of therapeutic interventions ^77,78^.
8. Kinesiophobia will be evaluated using the Tampa Scale for Kinesiophobia (TSK), a questionnaire developed to measure fear of movement and avoidance of physical activity in individuals with chronic pain. The Spanish version has been validated in a reduced 11-item format (TSK-11), assessing two factors: Avoidance of Activity (AA) and Harm (H). Each item is rated on a scale from 1 (strongly disagree) to 4 (strongly agree), yielding a total score ranging from 11 to 44, where higher values reflect greater kinesiophobia. Its test-retest reliability is moderate to high (Cronbach’s α = 0.79–0.81; ICC = 0.55–0.91) and shows significant associations with catastrophizing, anxiety, and depression. The TSK-11 is widely used in fibromyalgia and chronic pain research, serving as a key instrument to evaluate the impact of fear of movement on functionality and adherence to exercise-based treatments ^58,79,80^.
9. Lower-limb strength and endurance will be assessed using the 30-Second Sit-to-Stand Test (STS-30), a functional test that measures one’s ability to rise repeatedly from a chair over 30 seconds without using the arms. It is widely used to evaluate muscular strength, endurance, and functionality in individuals with chronic pain and reduced mobility. The total number of repetitions completed reflects functional performance, with higher scores indicating greater capacity. Test-retest reliability is high (ICC = 0.84–0.96), and the Spanish version has been validated in fibromyalgia and aging studies, making it essential for assessing functionality and progression in exercise-based intervention programmes ^81–83^.
10. Functional mobility will be assessed using the Timed Up and Go (TUG) Test, a widely used measure of walking speed, dynamic balance, and functional capacity in individuals with fibromyalgia. It involves timing how long it takes a participant to stand from a chair, walk 3 meters, turn 180 degrees, walk back, and sit down again. Its test-retest reliability is high, with an ICC of 0.935 when using a manual stopwatch and 0.955 when using an automatic device; the latter is recommended to improve precision and reduce variability in measurement. The TUG has been previously evaluated and validated in fibromyalgia patients and serves as a key tool for assessing clinical progression and the response to exercise-based therapeutic interventions ^46,84,85^.
11. Isometric quadriceps strength will be evaluated using dynamometry, a technique widely employed to quantify neuromuscular function in individuals with fibromyalgia. A portable dynamometer will be placed at the ankle with the knee flexed at 90° to measure the maximum voluntary isometric contraction of the quadriceps muscle. In fibromyalgia patients, a significant reduction in muscle strength has been reported, potentially associated with fatigue, chronic pain, and decreased functional capacity. Quadriceps strength measurement is a key indicator of lower-limb functionality and disability risk in this population. The test-retest reliability of isometric dynamometry in fibromyalgia ranges from 0.85 to 0.96 (ICC), and its use has been validated in previous studies, providing an objective assessment of muscular response to exercise-based therapeutic interventions.
12. Handgrip strength will be assessed using manual dynamometry, a validated method for measuring isometric hand strength and a clinically relevant marker in individuals with fibromyalgia. Three maximal attempts will be conducted for each limb using a handheld dynamometer, following standardized protocols with the elbow flexed at 90° and the forearm in a neutral position. In fibromyalgia patients, handgrip strength can be reduced by up to 40% compared to healthy individuals, which correlates with decreased functionality, widespread pain, and fatigue. This reduction also reflects potential neuromuscular dysfunction and central sensitization—key features of fibromyalgia. Test-retest reliability is high (ICC = 0.85–0.98), and the measure has been validated in previous studies, serving as a key tool for monitoring changes in functionality and evaluating therapeutic intervention outcomes ^82,86^.
13. Exercise behavior regulation will be assessed using the Behavioral Regulation in Exercise Questionnaire-3 (BREQ-3), an instrument grounded in Self-Determination Theory that evaluates various types of motivation for exercise. It consists of 24 items distributed across six dimensions, allowing analysis of the degree of self-determination in physical activity. The Spanish version has been validated, demonstrating satisfactory reliability (Cronbach’s α = 0.81 for intrinsic regulation and 0.70 for amotivation) and a solid factorial structure, supporting its construct validity. Among individuals with fibromyalgia, motivation is critical for exercise programme adherence, influencing functionality and quality of life. Consequently, BREQ-3 is a fundamental tool for assessing these factors in the present study ^87^.
14. Participants’ experience with virtual reality (VR) will be evaluated using NPRS-11scales for nausea intensity and satisfaction, ensuring the intervention’s tolerability and acceptance. VR has demonstrated efficacy as a tool in chronic pain management, including fibromyalgia, and its use in this study will be monitored to ensure participants’ comfort. Additionally, an NPRS-11will be employed to measure perceived pain before and after each session, providing an objective assessment of treatment impact.
15. Fear-avoidance beliefs regarding pain will be evaluated using the Fear-Avoidance Beliefs Questionnaire (FABQ), a widely used instrument in fibromyalgia and chronic pain studies to measure the impact of fear on physical activity and work. It comprises 16 items divided into two subscales: physical activity (FABQ-PA) and work (FABQ-W), with responses scored from 0 (strongly disagree) to 6 (strongly agree). In individuals with fibromyalgia, higher FABQ scores have been associated with increased disability, greater pain, and lower adherence to exercise programmes. The Spanish version has been validated, demonstrating high test-retest reliability (ICC = 0.84 for FABQ-W and 0.80 for FABQ-PA) and good internal consistency (Cronbach’s α = 0.88 for FABQ-W and 0.79 for FABQ-PA). Moreover, factorial analysis confirmed its bidimensional structure, further consolidating its utility as a key tool for assessing the psychological impact of pain on functionality and recovery ^88^.
16. The extent of pain and symptom severity will be evaluated using the Widespread Pain Index (WPI) and the Symptom Severity Scale (SSS), instruments used in the diagnosis and monitoring of fibromyalgia in accordance with the American College of Rheumatology (ACR) criteria. The WPI measures the distribution of pain across 19 body regions (scored 0–19), while the SSS assesses the severity of symptoms such as fatigue, sleep disturbances, and cognitive problems (scored 0–12). Both instruments will be administered before and after the intervention to assess the treatment’s impact on pain distribution and symptom severity.
17. Body perception will be evaluated using the adapted version of the Fremantle Body Awareness Questionnaire (FBAQ-B), an instrument designed to identify distortions in body representation—a phenomenon documented in individuals with fibromyalgia. These distortions include sensations of disconnection, changes in body shape or size, and difficulty localizing body parts, which are linked to dysfunctions in somatosensory integration and central sensitization. The Spanish version of the FBAQ-B has been validated, demonstrating a unidimensional structure, high reliability (α = 0.82), and good test-retest reliability (ICC = 0.78), as well as both discriminant and convergent validity, thus effectively differentiating between patients and controls. Given that virtual reality (VR) has the potential to modulate these mechanisms by providing an immersive environment that enhances body awareness, its impact will be analyzed before and after the intervention. Evaluating these changes will help determine whether combining VR with therapeutic exercise improves sensory integration and reduces perceptual distortions, thereby providing novel insights into its potential in fibromyalgia management ^89,90^.

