IVR has thus emerged as an innovative therapeutic tool, not only for modulating pain perception but also for improving functionality in patients with FM ^57–59^. While extensive research has examined IVR in the context of exergames or as an adjunct after exercise, its simultaneous application during therapeutic exercise remains underexplored. Furthermore, the potential benefits of manipulating visual feedback in an IVR environment during a therapeutic exercise program for FM have yet to be thoroughly investigated.

To our knowledge, no existing studies have evaluated the impact of a therapeutic exercise program incorporating IVR with modified visual feedback on FM symptoms. Therefore, the primary goal of the present study is to determine the efficacy of an IVR system that adjusts the patient’s visual perception, creating the illusion of reduced bodily movement compared to actual movement during resistance training. This manipulation may enable an increased range of motion without heightening perceived effort or pain, thereby optimizing overall treatment efficacy.

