**5.3 Timing of Data Processing**

Data will be recorded at two distinct time points (t) throughout the study:

- t₀: Before the intervention
- t₁: Immediately after the intervention

All data will be stored and processed for the strictly necessary duration to complete the study, following these phases:

- **Data Collection and Processing:** Conducted during the intervention period of the study, ensuring that only authorized personnel have access to the information.
- **Storage and Analysis:** Data will be maintained for the time required for analysis and subsequent publication of results, with custody secured through appropriate security measures.
- **Completion and Disposal:** Once the study is concluded and legal retention periods have expired, the data will be anonymized or securely destroyed in accordance with current regulations.

At all times, participants will have the right to access, rectify, restrict, or delete their data as provided by data protection legislation.

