**6. Ethical Considerations**

This study will adhere to the CONSORT guidelines for Randomized Controlled Trials and will be evaluated by the Ethics Committee of CEU Cardenal Herrera University, ensuring compliance with all necessary ethical directives. In addition, the study will follow the principles outlined in the Declaration of Helsinki (2013) and Good Clinical Practice (GCP) standards, thereby ensuring the respect, safety, and well-being of the participants.

Fibromyalgia is a chronic condition that significantly impacts the quality of life of those affected. Consequently, any therapeutic intervention must be carefully designed to maximize benefits while avoiding unnecessary risks. In this study, both immersive virtual reality (IVR) and therapeutic exercise have been extensively researched and demonstrated to be safe in similar populations. Nevertheless, potential transient effects—such as mild fatigue or slight dizziness related to IVR—will be closely monitored to guarantee participant well-being.

All study subjects will receive detailed information about the objectives, methodology, potential benefits, and risks of the intervention. Informed consent will be obtained prior to participation, ensuring that individuals make a free and fully informed decision. Furthermore, participants will have the right to withdraw from the study at any time without any negative consequences.

Data processing will be conducted in full compliance with the Organic Law on Data Protection and Guarantee of Digital Rights (LOPD-GDD) and the General Data Protection Regulation (RGPD 2016/679), thereby ensuring both confidentiality and anonymity. The data will be securely stored on CEU Cardenal Herrera University’s servers, with access restricted exclusively to the principal investigators. Upon completion of the study, the data will be disposed of in accordance with established security protocols.

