**Ethical Justification**

This study complies with the principles established in the Declaration of Helsinki (2013) and adheres to Good Clinical Practice guidelines, ensuring the respect and protection of participants in every phase of the research.

The proposed intervention does not present significant risks for the participants, as both IVR and therapeutic exercise have proven to be safe for those with fibromyalgia. Although transient effects such as mild dizziness or discomfort during IVR exposure may occur, these will be monitored closely to ensure participant safety.

All procedures for data collection and handling will be conducted in accordance with the RGPD and LOPD-GDD, ensuring the confidentiality and anonymization of participant information. Participants will be provided with detailed information regarding the study and will sign an informed consent form prior to enrollment. They will also be assured of their right to withdraw from the study at any point without any adverse consequences.

This approach ensures that the research not only advances scientific knowledge regarding the effectiveness of virtual reality for fibromyalgia management but also rigorously protects the rights, well-being, and autonomy of all participants.

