**7. ANEXOS**

**ANEXO I: Fibromyalgia Impact Questionnaire Revised (FIQR).**

**ANEXO II: EQ-5D-5L**

**ANEXO III: Hospital Anxiety and Depression Scale (HADS).**

**ANEXO IV:** **Multidimensional Fatigue Inventory (MFI-20)**.

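### The tolerability ratings do not match the transient effects the protocol promises to monitor, and they have no counterpart in the exercise-only arm

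*Protocol*

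**What the plan says.** **What is measured.** Protocol section 4.9, item 14 presents "NPRS-11scales for nausea intensity and satisfaction" as the means of securing tolerability and acceptance, under the heading of participants' experience with VR. It gives no timing for these two scales. The same item adds a pain rating before and after each session. Section 4.8 states that, during each session, pain, "perceived exertion (RPE), and well-being associated with Virtual Reality will be recorded".

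**What is expected and promised.** Section 6 (Ethical Considerations) anticipates effects "such as mild fatigue or slight dizziness related to IVR" and promises close monitoring. The Ethical Justification says that "transient effects such as mild dizziness or discomfort during IVR exposure may occur" and again promises monitoring. Section 5.5 promises continuous monitoring of study participants for any adverse effect. It names no form, definition or responsible role.

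**When data are recorded.** Section 5.3 states: "Data will be recorded at two distinct time points (t) throughout the study", namely t0 and t1. Section 5.1 has trained assessors collecting data at those two visits.

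**The safety statement.** Section 6 says that IVR and "therapeutic exercise have been extensively researched and demonstrated to be safe in similar populations". The Ethical Justification concludes that the proposed intervention carries no significant risk because each component is safe. The Introduction says of IVR that "its simultaneous application during therapeutic exercise remains underexplored".

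**The concern.** A tolerability measure should cover the effects the investigators expect, and it should be asked the same way in both arms so that the effect of the added component can be separated from that of the shared one. Here both arms do the same exercise programme, and fatigue or dizziness can follow exercise as well as a headset. If only IVR participants are asked, and they are asked about nausea and not dizziness, the report can describe how VR users felt but cannot say whether the named effects were more frequent with IVR than without it.

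This has to be settled in the protocol. A later analysis plan can decide how to tabulate symptoms, but it cannot tabulate ratings that were never collected. What is asked, of whom and at which session must be fixed before the first session is run.

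**Working it through.** The plan gives no figure for tolerability, so the main check sets the text side by side.

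**Step 1: named effects against stated measures**

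| Effect | Named in the ethics sections | Scored around sessions | Scored at t0 and t1 | Control-arm counterpart |
|---|---|---|---|---|
| Dizziness | Twice (section 6; Ethical Justification) | No | No listed outcome is stated to score it | None stated |
| Fatigue | Section 6 | No (RPE is exertion) | Yes, within SSS (item 16) and CSI (item 6) | Yes, but only at t0 and t1 |
| Discomfort | Ethical Justification | Possibly, through the undefined VR well-being record | No dedicated item | None; the record is tied to VR |
| Nausea | No | Timing not stated in item 14 | Not stated | None; the scale is tied to VR |
| Pain, exertion | Not named as IVR effects | Yes (4.8; pain also in 4.9, item 14) | Not needed here | Yes |

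Dizziness, the effect named most often, has no measure. The symptom that is scored, nausea, is not named in either ethics section.

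**Step 2: does the stated analysis reach item 14?** Section 4.10 analyses secondary outcomes by ANCOVA of t1 adjusted for t0, with Group as the factor. A rating of VR experience has no control group and no value before VR exposure, so that model cannot be applied to it.

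**Step 3: the recording schedule.** Sections 4.8 and 4.9, item 14 require recording at every session. The programme is 6 weeks × 2 sessions = 12 sessions. Section 5.3 recognises two recording times. The assessors of section 5.1 are blinded under 4.6 and 4.7, so they could not take VR ratings without learning the arm. No section says who keeps the session records or where they are entered.

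**Step 4: what a comparable record could show.** Inputs: target 80 (section 4.4), allocation 1:1 (section 4.6), so 80/2 = 40 per arm. With the 25% attrition of section 4.4, 40 × 0.75 = 30 remain.

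- Zero events among n participants, one-sided 95% upper bound: 1 − 0.05^(1/n). For n = 40: 1 − 0.05^(1/40) = 7.2%. For n = 30: 1 − 0.05^(1/30) = 9.5%.
- Power to detect a difference in the proportion with a symptom (two-sided 0.05, normal approximation, pooled variance under the null): Φ{[|q − p| − 1.96·√(2p̄(1−p̄)/n)] / √[(p(1−p) + q(1−q))/n]}, where p̄ = (p + q)/2. The documents give no symptom rates, so these are assumptions.

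| Control vs IVR (assumed) | 40 per arm | 30 per arm |
|---|---|---|
| 10% vs 20% | 24% | 19% |
| 10% vs 30% | 61% | 49% |
| 5% vs 30% | 85% | 73% |

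For 10% vs 30% at n = 40: (0.20 − 1.96 × 0.0894)/0.0866 = 0.285, and Φ(0.285) = 0.61.

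Only large differences would be seen, so descriptive reporting is the right use of such data.

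**The case against.** Much can be said for the plan as written.

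- **Fatigue is not ignored.** A reader might infer that it is never scored. It is: the SSS and CSI cover it in both arms at t0 and t1, and section 4.10 compares secondary outcomes by group. Only the session-level rating is absent.
- **Controls are not without data.** A reader might infer that they offer no comparison at all. Pain and exertion are recorded per session in the programme both arms follow, and the monitoring in section 5.5 is not limited to one arm. This stands. The gap is confined to the named transient effects.
- **Safety is not an objective.** Section 3 lists pain, quality of life and function, and central sensitization. This stands and limits the weight of the point. The protocol nevertheless commits itself to tolerability in item 14 and to monitoring in the ethics sections.
- **Other documents may fill the gap.** Case report forms and any analysis plan are not shown, and section 5.3 may be meant as the assessor visits only. That is a fair reading of the intent, but the literal texts conflict. Tabulation rules elsewhere would not by themselves add a dizziness question or a control-arm rating.
- **The Introduction's novelty claim is about efficacy.** It is hedged, and the reference list includes a trial titled as fully immersive VR combined with exercise in fibromyalgia. It therefore does not show the combination to be unsafe. It shows only that the modified visual feedback is new, which is reason not to extend component-level reassurance to it.
- **Unblinded self-ratings would not settle attribution.** True, since participants know their arm (section 4.6). This argues for cautious reporting, not for asking one arm only.

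**Conclusion.** The point holds as a cheap improvement. The stated tolerability ratings do not match the transient effects the protocol names. Dizziness is unscored, fatigue is unscored around sessions, the VR-tied ratings have no control counterpart, and the promised monitoring has no stated record. As written, those effects cannot be compared between arms. Section 5.3 also needs reconciling with sections 4.8 and 4.9.

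A reader might go further and conclude that the trial cannot show whether adding IVR is safe. The documents do not support putting it that way. Safety is not among the objectives, some per-session data are comparable, and general monitoring is promised for all participants. Nor would a better form establish safety at this size: with no events in 40 IVR participants, risks up to about 7.2% remain compatible with the data (9.5% if 30 remain).

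The primary outcome, its analysis and the sample size are untouched. The conclusion assumes that item 14 and the well-being record apply to VR users only, as their wording implies, and that no form outside the protocol already collects these symptoms in both arms. The power figures rest on assumed symptom rates.

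**What to change.** 1. In 4.8 and 4.9, item 14, have the session researcher complete one identical short form in both arms at every session. It should hold 0-10 ratings of nausea, dizziness and fatigue beside the existing pain and RPE ratings, and one open question on any unwanted event, including falls. State whether the ratings are taken once or before and after the session.
2. Keep VR satisfaction and well-being as descriptive items for the IVR arm, outside the ANCOVA of 4.10.
3. In 5.1 and 5.3, add the 12 session records to the data schedule, name who completes and enters them, and keep them from the blinded assessors. This also resolves the conflict over two recording times.
4. Report symptoms and events by arm descriptively, noting that ratings are unblinded and that only large differences could be seen.
5. In the Ethical Justification, limit the no-significant-risk statement to the separate components and say that tolerability of the combination is being recorded.

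**Cost.** Three ratings per session, or six if taken before and after: 3 × 12 = 36 to 6 × 12 = 72 per participant over the programme, plus one question and the data entry. A researcher already leads each session and pain and exertion are already recorded there. Treatment, sample size and primary analysis do not change.

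The MFI-20 is annexed without an entry in 4.9. That is a separate clerical matter: list it as an outcome or remove the annex.
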